### Sample size

On the basis of previous observational data on recovery after surgery for colon cancer in Swedish patients, an initial sample size was calculated as 370 patients. Previous knowledge about the possible effect of this type of physical activity is scarce, however, and the assumptions underlying the sample size were associated with uncertainty. An interim sample size recalculation was decided to be performed after 6 months of follow-up data were available for the first 100 patients. The aim of the analysis was to obtain preliminary estimates of the rates of the two primary outcome measures—patient-reported physical recovery and sick leave—in the groups, as well as an effect size to enable a sample size re-estimation.

An external independent data monitoring committee consisting of two physicians and a statistician performed the interim analysis on data where information about the true type of intervention was concealed. After 100 patients were included, 77 patients had data on physical recovery 4 weeks post-operatively, with 49% and 37% feeling highly physically recovered in the two groups (i.e., a relative difference of 32%). For true rates of these magnitudes, a difference will be detected with 80% power using a total of 640 patients and a two-sided test with a 2.5% significance level (Bonferroni adjustment for interim look). After the interim analysis, sick leave was no longer considered a primary outcome measure, and physical recovery remained the sole primary outcome measure. The study is planned to continue until 640 patients are included, given the observed frequency of withdrawn consent and other reasons for discontinuation.

Given the nature of the intervention, with no anticipated serious side effects, and with patients generally willing to do what they can to improve their cancer prognosis, we assume that the rate of enrolment of patients will be high. All medical staff working in participating departments of surgery will receive information about the study to further enhance possibilities of adequate participant enrolment. All patients planned for colorectal cancer surgery at participating hospitals will receive a telephone call with oral information as well as written information about the study before their pre-operative visit, as well as oral information provided by a research nurse at their pre-operative outpatient visit.

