**Methods/design:**

We are conducting a randomised, controlled, parallel-group, open-label, multi-centre trial with physical recovery within 4 weeks after cancer surgery as the primary endpoint. Some 640 patients planned for surgery for colorectal cancer will be enrolled. The intervention consists of pre- and post-operative physical activity with increased daily aerobic activity of moderate intensity as well as IMT. In the control group, patients will be advised to continue their normal daily exercise routine. The primary outcome is patient-reported physical recovery 4 weeks post-operatively. Secondary outcomes are length of sick leave, complication rate and severity, length of hospital stay, re-admittances, re-operations, post-operative mental recovery, quality of life and mortality, as well as changes in insulin-like growth factor 1 and insulin-like growth factor-binding protein 3, perception of pain and a health economic analysis.

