### Allocation

A research nurse will perform enrolment and the electronic randomisation. The trial is an open-label study because neither patients nor research nurses nor physiotherapists can be blinded. However, registration regarding complications, hospital length of stay, re-operations, re-admittances, mortality and sick leave will be blinded. The nurses and surgeons responsible for providing care during the hospital stay are not actively informed about allocation. Randomisation will be performed as block randomisation with a 1:1 allocation and a block size that will be unknown to study personnel. To ensure good balance of participant characteristics in each group, randomisation will be stratified with regard to surgical method (laparoscopic versus open), tumour site and pre-operative treatment (colon, rectum with/without radiotherapy), and study centre. Randomisation numbers (patient numbers) will be assigned strictly sequentially as patients become eligible for randomisation. The assigned group is automatically generated and cannot be changed retrospectively.

The screening log and randomisation process is part of an electronic clinical record form in which inclusion and exclusion criteria are noted, as well as information needed for stratification. All patients planned for elective colorectal surgery at participating hospitals are included in the screening log. Patients excluded will be included in the screening log with information on age, sex and reason for exclusion.

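### 640 is the number with outcome data needed for 80% power, yet it is also the number to be included, so the stated inputs leave no allowance for loss

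*Protocol article*

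**What the plan says.** All the figures come from the protocol article.

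- **Rates.** The re-estimation in the Sample size section uses the interim results, "with 49% and 37% feeling highly physically recovered in the two groups".
- **Level.** The test is "a two-sided test with a 2.5% significance level (Bonferroni adjustment for interim look").
- **Power.** The claim is that "a difference will be detected with 80% power using a total of 640 patients and a two-sided test with a 2.5% significance level".
- **Recruitment target.** The same paragraph ends: "The study is planned to continue until 640 patients are included, given the observed frequency of withdrawn consent and other reasons for discontinuation". The abstract agrees that 640 is a recruitment number: "Some 640 patients planned for surgery for colorectal cancer will be enrolled".
- **Completeness at the interim.** Of the first 100 patients included, "77 patients had data on physical recovery 4 weeks post-operatively".
- **Allocation.** The Allocation section states "Randomisation will be performed as block randomisation with a 1:1 allocation".

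No assumed loss rate is given, and no evaluable number is stated apart from the 640 included.

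**The concern.** A sample-size formula for two proportions returns the number of patients who contribute an outcome. If some included patients have no 4-week questionnaire, the included number must exceed the evaluable number by the expected loss. Here one figure serves as both, while the text says that withdrawal and discontinuation were taken into account. If 640 is what the formula gives before any loss, that statement is wrong and the 80% does not describe the trial as planned.

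This is the sole primary endpoint, and the re-estimation was done because the assumptions behind the first target were uncertain. A null result would be read as coming from a trial with 80% power for a 12-point difference when its power was lower.

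**Working it through.** **Inputs** (Sample size and Allocation sections): p1 = 0.49, p2 = 0.37, difference 0.12; two-sided level 0.025, so z = 2.2414; power 80%, so z = 0.8416; 1:1 allocation. Completeness at the interim: 77/100 = 0.77.

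**1. Reproducing 640**

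Unpooled variance:

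n per arm = (2.2414 + 0.8416)² × (0.49×0.51 + 0.37×0.63) / 0.12²
= 9.505 × (0.2499 + 0.2331) / 0.0144 = 318.8, so 319 per arm and 638 in total.

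Pooled variance, with mean rate 0.43:

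n per arm = [2.2414×√(2×0.43×0.57) + 0.8416×√(0.2499 + 0.2331)]² / 0.0144 = 322.3, so 323 per arm and 646 in total.

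The arcsine formula gives 644. The published 640 therefore reproduces, but only as a number with complete outcome data.

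**2. Power at exactly 640 evaluable**

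Power = Φ{[0.12×√n − 2.2414×√(2×0.43×0.57)] / √(0.2499 + 0.2331)}

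With n = 320 per arm: Φ[(2.1466 − 1.5693)/0.6950] = Φ(0.831) = 79.7%. Nothing is left over for loss.

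**3. Could 640 already be an inflated number?**

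- At a two-sided 5% level the pooled formula gives 534. Inflated for 23% loss, this is 534/0.77, or 694, which is not 640 and contradicts the stated 2.5%.
- Multiplying 534 by 1.2 gives 641, but this needs a different significance level and also an incorrect inflation (multiplying by 1 + loss instead of dividing by 1 − loss).
- With a continuity correction, the stated inputs need 678, which is more than 640.

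None of these routes fits the stated inputs.

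**4. Power with 640 included, by loss**

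The formula of step 2 with n = 320 × (1 − loss) per arm:

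| Loss | Evaluable in total | Power |
|---|---|---|
| 0% | 640 | 79.7% |
| 5% | 608 | 77.4% |
| 10% | 576 | 74.9% |
| 15% | 544 | 72.2% |
| 20% | 512 | 69.3% |
| 23% | 493 | 67.4% |

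For the last row, n = 246.4 per arm: Φ[(1.8837 − 1.5693)/0.6950] = Φ(0.452) = 67.4%.

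**5. Detectable difference at 23% loss**

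Holding the lower rate at 37% and solving for 80% power with about 493 evaluable gives about 13.7 percentage points, against 12 at 640.

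**6. Number to include if 80% were to be kept at 23% loss**

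640/0.77 = 831.2, so 832; from the pooled figure, 646/0.77 = 839. At 10% loss the corresponding numbers are 712 and 718.

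**7. Sensitivity of the 67%**

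Rounding in the two published rates (48.5–49.5% and 36.5–37.5%) moves power at 493 evaluable over about 59% to 75%, always below 80%. At a two-sided 5% level, which the protocol does not use, it would be 76.9%.

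**The case against.** A reader might infer that the 23 patients without data are all lost and that the true power of the trial is two thirds. The article does not support either as a fact.

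- **Reasons for the 23.** None is given. The 6-month follow-up on the first 100 patients is stated as the plan for the look; no date of the actual data cut is reported, and the result is introduced only as coming after 100 inclusions. With about two weeks of pre-operative intervention before surgery and an outcome four weeks after it, some recent inclusions could have been pending. If the look took place as planned, it is unlikely that most were, but it is not excluded.
- **What 67% assumes.** Interim completeness must hold throughout, and patients without 4-week data must add no information. The Statistical methods section specifies generalised linear models adjusted for the stratification factors and defers detail to an analysis plan that is not shown. Adjustment or the handling of missing data could recover some power, which the two-proportion calculation does not credit.
- **Uncertainty of the effect.** The 12 points come from 77 patients. At about 38 per arm the standard error is √[(0.2499 + 0.2331)/38.5], or about 11 points. Any power figure is conditional on that difference being true, and this uncertainty is larger than the effect of attrition.
- **The calculation of 640 is itself correct.** The fault is in the use of the number.

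These points stand and limit the claim to a conditional one. They do not rescue the text. The protocol itself says that withdrawal and discontinuation were observed, so zero loss is ruled out by its own words, and at the stated inputs any loss takes power further below 80%. Analysis by intention to treat does not supply a questionnaire answer that was never given, and the stated 80% credits no method for doing so.

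**Conclusion.** The point holds as an internal inconsistency. At 49% versus 37%, a two-sided 2.5% level and 80% power, 640 is the number of patients with observed 4-week data. The Sample size section and the abstract make it the number included or enrolled, and the statement that it takes account of withdrawals has no counterpart in the stated inputs.

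The size depends on loss that the article does not establish: a shortfall of about 3 percentage points from the stated 80% at 5% loss, about 5 at 10%, and about 13 if completeness of 77 in 100 persists. The last is a projection under the assumptions named above. That 640 contains no allowance for loss is certain at the stated inputs; how far the power falls is not.

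**What to change.** In the Sample size section:

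1. State that 640 is the evaluable number for 80% power at the given rates and level.
2. Delete the statement that including 640 already takes account of withdrawn consent and discontinuation.
3. Report how many of the first 100 patients lacked the 4-week outcome because of withdrawal, discontinuation, non-response or data still pending.
4. Restate the power for 640 included at the loss so found, with the range. At 23% loss: about 493 evaluable, power about 67% for 49% versus 37%, and 80% power only for a difference of about 13.7 points with the lower rate at 37%.

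This is a change of wording plus a tabulation of interim data already held. It requires no added enrolment and leaves randomisation, endpoint and significance level as they are. The cost is a less favourable stated power. If the sponsor prefers to keep the 80% claim for 640 included, the protocol would have to show the calculation that supports it, including the loss assumed.

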### Data collection

Data collection will be performed at the following times:The pre-operative case report form (CRF) is filled out by a nurse using data collected at inclusion. This includes characteristics of importance for post-operative recovery, such as weight; length; and basic clinical information such as haemoglobin, leucocyte count, C-reactive protein (CRP), serum albumin, serum creatinine and analyses of circulating levels of IGF-1, IGFBP-3 and HbA1c (*see* below). It also includes data on pre-operative MIP (measured as centimetres of water) for patients in the intervention group.IGF-1 and IGFBP-3 will be analysed at inclusion, before the start of anaesthesia and 4–6 weeks post-operatively in a sub-group of patients. IGF-1 will be analysed using an IDS-iSYS (Immunodiagnostic Systems, Tyne & Wear, UK), and IGFBP-3 will be analysed using an IMMULITE 2000 XPi (Siemens Medical Solutions, Malvern, PA, USA). HbA1c will be analysed before the intervention and 4–6 weeks post-operatively in a sub-group of approximately 80 patients at one hospital. Analysis of HbA1c is conducted by high-performance liquid chromatography (ion exchange liquid chromatography) with the Mono-S 5/50 GL Tricorn column (GE Healthcare Bio-Sciences, Uppsala, Sweden).At discharge from hospital, a CRF is filled out with information on hospital length of stay, possible time of stay in the intensive care unit, blood transfusions, post-operative haemoglobin, leucocyte count, CRP and destination after discharge.Patient files will be examined to classify adverse events according to the Clavien-Dindo classification of surgical complications [47] for the first 90 days post-operatively by one or two doctors per site without access to group denomination for each patient.All included patients will be asked to fill out questionnaires at inclusion, 4 weeks post-operatively and 12 months post-operatively. These will include the following validated questionnaires: IPAQ [35], Saltin-Grimby Physical Activity Level Scale [36], RAND-36 [42], EQ-5D [44], sense of coherence [48], general QoL questions from previously used questionnaires [49, 50], AUDIT-C [46], BPI-SF [34], pack-years of smoking and questions about patients’ perceived level of recovery, re-admittances and re-operations.Data will be retrieved from the Swedish Social Insurance Agency regarding length, degree and reason for sick leave during the first 12 post-operative months. Patients in occupation or seeking work will be offered 3 weeks of sick leave at hospital discharge. A prolongation by 1 week at a time until visit at the outpatient clinic will be granted at the request of the patient by way of a telephone call to an answering machine.Clinical data and TNM classification will be retrieved from the Swedish National Colorectal Cancer Registry, in addition to data on mortality 3 and 5 years post-operatively.Complications and adverse events due to the intervention will be registered and analysed.

For participant time lines, *see* Fig. 1. For a Standard Protocol Items: Recommendations for Interventional Trials (SPIRIT) diagram showing all data collection and the respective time points, *see* Fig. 2. All CRFs and questionnaires (in Swedish) can be obtained from the corresponding author upon request. Patients who wish to be excluded from the study will be asked if data already collected may be analysed in the study.

**Fig. 1 Fig1:**
[figure not shown]
Participant time line. Time schedule of enrolment, intervention, assessments and visits for participants. *CRF* Case report form, *HbA1c* Glycated haemoglobin, *IGF-1* Insulin-like growth factor 1, *IGFBP-3* Insulin-like growth factor-binding protein 3

**Fig. 2 Fig2:**
[figure not shown]
Standard Protocol Items: Recommendations for Interventional Trials (SPIRIT) figure showing important events in the trial and their respective time points. *Hb* Haemoglobin, *WBC* White blood cells, *ASA* American Society of Anesthesiologists physical status, *BPI-SF* Brief Pain Inventory–Short Form, *CRP* C-reactive protein, *HbA1c* Glycated haemoglobin, *IGF-1* Insulin-like growth factor 1, *IGFBP-3* Insulin-like growth factor-binding protein 3, *IPAQ* International Physical Activity Questionnaire

### Data management

All patients receive a study number, and the identification key is kept separately from the results database on a server at Sahlgrenska University Hospital. Data will be entered manually from paper CRFs into a central database on a server at Gothenburg University, where automatic back-up of server data as well as firewalls against external violation are present. A range check will be performed on applicable variables. Laboratory samples will be analysed locally. The occurrence of relevant protocol deviations will be determined and documented. Data verification and validation will be performed. When all data have been coded, validated, signed and locked, a clean file will be declared. A data manager will be responsible for the database.

### Statistical methods

The primary analyses of patient-reported physical recovery as well as sick leave, length of hospital stay and complications will be analysed on an intention-to-treat basis with generalised linear models with group as fixed effects and stratification factors as covariates. Multiplicity correction will be performed to prevent inflation of the family-wise error rate. A detailed statistical analysis plan will be finalised before any data are analysed.

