### Outcomes

The primary endpoint is physical recovery as measured by patient-reported experienced physical recovery. Patient-reported physical recovery will be assessed by questionnaires 4 weeks and 1 year post-operatively, with the question, “To what extent do you feel fully physically recovered”? Answering categories are 0%, 25%, 50%, 75% and 100%. This question has been validated face-to-face and has previously been used in several cohort studies [28–30].

Secondary endpoints are as follows:
*Sick leave:* This will be measured by length and degree of sick leave, for all causes, during the first year post-operatively.
*Adverse events classified according to the Clavien-Dindo classification of surgical complications* [31] *within the first 90 days post-operatively:* These will be reported as the number of complications grade O-IIIa and IIIb-V. We will also report information gained from the comprehensive complications index for all patients, which is derived from the Clavien-Dindo classification [32].
*Length of hospital stay*

*Post-operative recovery of QoL measured with several instruments pre-operatively and 4 weeks and 1 year post-operatively:* Quality-adjusted life-years (QALYs) will be possible to calculate because EQ-5D is included in the questionnaire [33].
*Re-operations and re-admittances within the first 12 months after primary surgery:* All forms of surgery and all re-admissions to hospital will be registered.
*Patient-reported experienced mental recovery 4 weeks and 12 months post-operatively, used in previous observational cohort studies* [28–30]
*Post-operative all-cause and cancer-specific mortality, measured at 3 and 5 years*

*Changes in IGF-1, IGFBP-3 and glycated haemoglobin (HbA1c) levels from baseline to time of surgery (IGF-1 and IGFBP-3) and 4–6 weeks after surgery (all):* These will be determined for a subgroup of the patients and analysed prior to the rest of the outcomes.
*Post-operative pain measured with Brief Pain Inventory–Short Form (BPI-SF):* This will be measured 4 weeks and 12 months post-operatively [34].
*Health economic analysis of resource consumption 12 months post-operatively:* This will be performed separately, depending on other outcomes.

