## Discussion

Pre-operative lifestyle interventions are receiving increased interest because of the multiple possible positive effects of physical activity [9]. In this study, we hypothesise that patients undergoing surgery for colorectal cancer will benefit from pre-operative physical activity for several reasons. Firstly, the patients are generally old, and a high proportion of the patients can be suspected to be physically active to a lesser degree than recommended [52], thereby having lower endurance capacity, strength and functional capacity than active individuals. Patients with poor functional capacity have a higher risk of a poor post-operative recovery [53]. Secondly, in parallel with their age, more of these patients can also be expected to have other diagnoses for which physical activity shows evidence of positive effects, such as hypertension, diabetes mellitus and hyperlipidaemia as well as established cardiovascular disease [9]. In addition, receiving a cancer diagnosis usually affects the mental well-being of the patient, and physical activity may possibly distract the patient’s thoughts from the disease because it has established positive effects on stress-related and mental health [9]. A further possible effect could be an increased sense of control as in ‘I do what I can to improve the outcome of the treatment’. Finally, there may be positive effects on the immune system that would be beneficial for post-operative recovery [10].

This is the first study of prehabilitation before colorectal surgery primarily aiming to include estimation of clinically relevant outcomes such as physical recovery, sick leave, hospital length of stay and adverse events. All patients in Sweden are covered by a national health insurance programme administered by the Swedish Social Insurance Agency. This, combined with accessible and reliable data on sick leave, makes length of sick leave/return to work one valuable measurement of recovery. Because almost 75% of patients with colorectal cancer have reached retirement age, another measure of physical recovery that reflects the effect of the intervention in the entire population is our primary outcome measure.

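### The primary model adjusts only for the stratification factors and leaves unused the precision in baseline function and activity measures that are already being collected

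*Protocol article*

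**What the plan says.** The Statistical methods section of the protocol article names the model for physical recovery, sick leave, length of stay and complications: "generalised linear models with group as fixed effects and stratification factors as covariates". It names no other covariate and says that a detailed analysis plan will follow. The stratification factors are given under Allocation: "randomisation will be stratified with regard to surgical method (laparoscopic versus open), tumour site and pre-operative treatment (colon, rectum with/without radiotherapy), and study centre".

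On baseline data, the Data collection section says: "All included patients will be asked to fill out questionnaires at inclusion, 4 weeks post-operatively and 12 months post-operatively". The instruments listed there include IPAQ, the Saltin-Grimby scale, RAND-36 and EQ-5D. The same section describes the pre-operative case report form in these terms: "This includes characteristics of importance for post-operative recovery, such as weight; length; and basic clinical information such as haemoglobin". In the Discussion the authors write: "Patients with poor functional capacity have a higher risk of a poor post-operative recovery".

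The primary outcome is one self-reported question with five ordered answers (Outcomes). The sample size treats it as binary, using "49% and 37% feeling highly physically recovered in the two groups".

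**The concern.** The covariates in the model describe the operation, the tumour and the hospital. None describes how fit or active the patient was beforehand. For an outcome of self-reported physical recovery, prior function and activity are natural prognostic variables, and the protocol says as much about functional capacity. The recovery question can have no baseline value of its own, so the inclusion questionnaires hold the closest available proxies.

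Adjusting for a prognostic baseline variable narrows the confidence interval for the treatment effect and removes the influence of chance imbalance in that variable. At stake is some power that could be had without recruiting anyone or collecting anything further.

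**Working it through.** **Inputs from the Sample size and Allocation sections.** Rates 49% and 37% (difference 0.12), two-sided 2.5% level, 80% power, 640 patients in total, 1:1 allocation. At the interim look, 77 of the first 100 patients had the 4-week outcome.

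**Input not in the documents.** R², the share of outcome variance explained by the added covariates beyond the strata. It is assumed here to lie between 2% and 20%.

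**Step 1: reproduce 640.** Normal quantiles are 2.2414 (two-sided 2.5%) and 0.8416 (80% power).
- Unpooled variance: 0.49×0.51 + 0.37×0.63 = 0.483. Per arm, n = 0.483 × (2.2414 + 0.8416)² / 0.12² = 318.8, so 319 per arm and 638 in total.
- Pooled variance under the null: mean rate 0.43, 2×0.43×0.57 = 0.4902. Per arm, n = (2.2414×√0.4902 + 0.8416×√0.483)² / 0.12², which rounds up to 323, or 646 in total.

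The planned 640 lies between these. Power at 320 per arm (pooled) is Φ[(0.12×√320 − 2.2414×√0.4902)/√0.483] = 79.7%. The figure is therefore that of an unadjusted comparison of two proportions and takes no credit for covariates.

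**Step 2: add covariates.** To a linear approximation, adjustment multiplies the variance by (1 − R²), so the effective sample size is n/(1 − R²). With 77% availability, 640 × 0.77 = 492.8, about 493 analysed. Power by the pooled formula:

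| Assumed R² | Effective N of 640 | Power, 640 analysed | Power, about 493 analysed |
|---|---|---|---|
| 0 | 640 | 79.7% | 67.4% |
| 0.02 | 653 | 80.6% | 68.4% |
| 0.05 | 674 | 81.9% | 69.9% |
| 0.10 | 711 | 84.1% | 72.5% |
| 0.15 | 753 | 86.3% | 75.2% |
| 0.20 | 800 | 88.4% | 78.0% |

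With the unpooled variance, the values for 493 analysed are 68.1% at R² = 0, then 70.5%, 73.1%, 75.8% and 78.5% at R² = 0.05, 0.10, 0.15 and 0.20. The two formulas together give the range of 67-68% rising to 70-79%.

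**Step 3: check the approximation in a logistic model.** Logistic regression with one prognostic covariate was simulated, 2,000 trials per setting, holding the marginal rates at 37% and 49%:

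| R² | 320 per arm, unadjusted → adjusted | 246 per arm, unadjusted → adjusted |
|---|---|---|
| 0 | 79.95% → 80.1% | 68.35% → 68.2% |
| about 0.02 | 79.85% → 80.9% | 67.85% → 68.9% |
| about 0.05 | 79.7% → 81.95% | 69.0% → 71.0% |
| about 0.105 | 79.2% → 84.3% | 67.0% → 71.7% |
| about 0.16 | 80.45% → 88.5% | 67.6% → 75.25% |

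The gain is not an artefact of the linear formula. A covariate with no prognostic value costs essentially nothing at these sample sizes.

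**The case against.** The strongest objection is that this is a preference, not a defect. Adjusting for the stratification factors respects the randomisation and gives a valid test. The sample size is right for its own inputs. Further covariates could be added in the analysis plan, which is not shown. The first two parts stand: nothing here is an error. The third stands only in part. The article is not silent on covariates. It states the set, and a plan that follows it would carry the narrow set forward.

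The gain is also uncertain. The documents say that functional capacity is prognostic but not how strongly, and they do not tie RAND-36 or Saltin-Grimby to the 4-week question. At R² of 2% or less the gain is about one point. The calculation also treats as binary an outcome collected in five ordered categories. These limits stand, and they are why a range is given.

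Three practical points stand as well. Every patient is asked for the questionnaires, which is not the same as every patient returning them. The text does not say whether inclusion questionnaires are completed before allocation, which matters in an open-label trial. With a logistic or ordinal link, added covariates make the effect estimate conditional.

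A reader might infer more than the documents support in two ways:
- **That the trial falls short of its stated power.** This holds only if the 77 of 100 seen at the interim persists. With 640 analysed, power is 79.7%, and some of those 100 patients may not yet have reached week 4.
- **That the quality-of-life and pain outcomes also omit their own baseline values.** The model sentence does not cover RAND-36, EQ-5D or BPI-SF outcomes, so the article shows no such omission.

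**Conclusion.** The point holds as a missed gain in efficiency, not as a flaw in validity. The stated covariates contain no measure of baseline function or activity, although such measures are requested from all patients and the protocol regards functional capacity as prognostic.

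With all 640 analysed, power would rise from about 80% to about 81-88% for an assumed R² of 2-20%. If only about 493 have the 4-week outcome, it would rise from about 67-68% to 70-79% for an assumed R² of 5-20%. Both ranges rest on an R² that the documents do not give and on the binary form of the outcome used for sizing. The second also rests on the interim availability continuing. The change is worth making because it costs little, but the trial does not depend on it.

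**What to change.** Before any unblinded data are seen, state in the analysis plan that the primary model contains, beside group and the stratification factors:
- baseline RAND-36 physical functioning, as a continuous variable;
- one baseline activity measure, for example the Saltin-Grimby level;
- age.

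Use only values recorded before the patient's allocation is known, and confirm from the trial's procedures that the inclusion questionnaire meets this condition. Fill missing baseline values by a simple pre-specified imputation so that no randomised patient drops out of the analysis for lack of a covariate. If the link is logistic or ordinal, report a standardised (marginal) risk difference so that the effect measure stays interpretable.

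The cost is a few sentences of plan text, slightly more analysis work and a rule for missing baseline values. No new data collection is needed, and the sample size need not change.
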